### Therapist training

Six therapists working at the participating hospitals completed a 4-day training programme provided by a senior clinical psychologist (HK). The training consists of discussing each treatment module and practising the interventions in role-playing with simulation patients, being professional actors. An introduction to the online platform, exercises in writing e-mails and giving online feedback are part of the training. Five therapists working at the Expert Centre for Chronic Fatigue (ECCF) of the Amsterdam UMC were already trained in the protocol for CBT for CFS, but followed an additional 2-hour training programme on COVID-19-specific issues.

### Adherence and treatment integrity

All therapists are supervised bi-weekly by an experienced clinical psychologist (HK, TK) to ensure treatment integrity. In this supervision, all cases are discussed. Therapists register each face-to-face, video, phone and e-mail contact with the participant. The duration of the contact and treatment modules delivered are registered. All activities of the participant and therapist on the platform are registered via log data and are available for analysis.

### Care as usual

After randomisation, participants in the care as usual condition have no access to *Fit after COVID* during the study, but are not restrained from using any form of care for fatigue or other COVID-19 related symptoms. Care as usual for post-COVID-19 patients can entail follow-up contacts with their treating physician or GP, physical training, occupational therapy or rehabilitation. At T1, all participants are questioned about the care they received since baseline assessment. Participants who are still severely fatigued, i.e. a score of ≥ 35 on the CIS-fatigue at T2, and voice a care need can be referred for CBT for severe fatigue; this will be provided by the ECCF of the Amsterdam UMC.

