### Recruitment 

Patients are recruited by medical professionals of participating hospitals in the Netherlands: Amsterdam University Medical Centers (Amsterdam UMC), location Academic Medical Center (AMC) and VU medical center (VUmc) in Amsterdam, Radboud university medical center (Radboudumc) in Nijmegen, Jeroen Bosch Hospital (JBZ) in Den Bosch, Catharina hospital in Eindhoven and Bernhoven in Uden. In addition, general practitioners (GP’s), public health services, patient organisations and the general public are informed about the study by flyers, leading to referrals via GP’s and self-referrals. For recruitment via self-referral, the study is advertised via social media, i.e. LinkedIn and Facebook, and adverts in local newspapers. Additionally, a study-website (www.moenacovid.nl) has been developed, where interested individuals can find information about the study, fill out a brief test to check whether they fulfil inclusion criteria, and find information on how to contact the research assistant.

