After obtaining informed consent, online screening questionnaires are administered by the researcher to verify the remaining eligibility criteria (see Table 1). The subscale fatigue severity of the CIS-questionnaire [38] is used for inclusion criterion c, to screen for the presence of severe fatigue. For inclusion criterion d, the presence of limitations in physical or social functioning, the subscale physical functioning of the Short Form Health Survey (SF-36) [40] and the Work and Social Adjustment Scale (WSAS) [41] are used. Participants are screened for the presence of post-traumatic stress disorder (PTSD) with the PTSD Checklist for DSM-5 (PCL-5) [42], and for the presence of a depressive disorder with the Beck Depression Inventory for Primary Care (BDI-PC) [43, 44] (exclusion criterion a, i.e. the presence of a psychiatric condition that can explain the fatigue). If the score on the BDI-PC is ≥ 4 or the score on the PCL-5 is ≥ 33, the Mini-International Neuropsychiatric Interview (M.I.N.I.) [45] is conducted by a trained research assistant via phone to determine if patients meet the criteria of a depressive disorder or PTSD. In that case, patients will not be included. Instead, the GP is contacted for referral to appropriate treatment. If two persons from the same household are screened and found to be eligible, only one of them can participate (based on their choice). This is to prevent contamination. The other person is allocated to the same condition outside the study context. If a patient has been infected twice, the first diagnosis with COVID-19 or hospital discharge must be from 3 months up to and including 12 months ago (inclusion criterion a). Only in those cases where fatigue commenced or increased substantially directly after the second infection, the second infection is used as the reference point to determine eligibility.

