### Procedure 

Eligible and consenting participants start with the baseline assessment (T0). Following T0, participants are randomised to the CBT group or care as usual. In case of randomisation to CBT, the first treatment session is planned within 2 weeks after randomisation. Nineteen weeks after randomisation all participants are assessed again (T1). For participants assigned to CBT this is the post-intervention assessment. At follow-up (T2), 6 months after T1, all participants are assessed again. Participants randomised to the CBT group are also assessed at long-term follow-up (T3), 12 months after treatment. Due to ethical considerations, participants from the care as usual arm are offered referral for existing CBT for chronic fatigue after the follow-up assessment (T2) and hence, cannot serve as a control for the long-term follow-up assessment. A flow-chart of the study design is shown in Fig. 1.

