### Randomisation

Allocation of participants to either CBT or care as usual is stratified based on (1) illness severity during the acute stage of COVID-19 (no admission to hospital; admitted to hospital, not on the intensive care unit (ICU); ICU during hospitalisation) and (2) dyspnoea based on the Medical Research Council (MRC) [59] score (< 3 vs. ≥ 3). This is because dyspnoea might influence the response to CBT by interfering with the graded activity module. A web-based randomisation programme in Castor EDC [60] is used to generate the randomisation sequence. The allocation ratio is 1:1. Block-randomisation with randomly selected block sizes (i.e. 2, 4 or 6) is used. The randomisation is performed by a research assistant in the presence of the participant who is on the phone. The research assistant, the researcher and the participants are blinded to the allocation sequence. Due to the nature of the intervention, blinding to allocation is not feasible. Data will be analysed by an independent statistician using a data file which is blinded for treatment allocation.

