### Outcome measures

Outcome measures consist of self-reported questionnaires, which are assessed at T0, T1, T2 and T3. See Table 3 for the measurements at all time points. The questionnaires are administered online using Castor EDC [60]. Participants receive an e-mail with a personal link to fill out the questionnaires. For optimal retention, participants are contacted by the research assistant if they have not completed the questionnaires within one week. When participants are not willing to complete all measurements at T1, T2 and/or T3, they are asked to at least fill out the CIS-fatigue [38], which is the primary outcome measure. At T0 and T1, data on physical activity level and sleep are also gathered by using an actigraph and completing a sleep diary.

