### Primary and secondary objectives

The primary objective is to investigate whether CBT will lead to a significantly lower mean fatigue severity score measured with the CIS-fatigue across follow-up visits T1 and T2 as compared to care as usual.

Secondary objectives are to investigate whether CBT as compared to care as usual will result in:
A smaller proportion of patients meeting the cut-off score for severe fatigue (i.e. caseness as defined by a CIS-fatigue score of ≥ 35) at follow-up assessments T1 and T2 separately;A higher proportion of patients no longer meeting the cut-off score (as defined in a) and additionally, reporting a clinical significant change (i.e. Reliable Change Index (RCI)) [84] in fatigue severity at follow-up assessments T1 and T2 separately;A smaller proportion of patients with chronic fatigue (i.e. caseness as defined in a) and self-reported duration of fatigue of 6 months or longer at T1 and T2 separately;Significantly higher mean physical functioning as assessed with the SF-36 across follow-up assessments (T1 and T2);Significantly lower mean level on the WSAS across follow-up assessments (T1 and T2);Significantly lower mean level of somatic symptoms as assessed with the PHQ-15 across follow-up assessments (T1 and T2); andSignificantly lower mean level of cognitive symptoms as assessed with the subscale concentration problems of the CIS across follow-up assessments (T1 and T2).

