To explore the robustness of our findings from the primary analysis, four sensitivity analyses will be conducted. First, per protocol analysis will be conducted. Treatment completion will be operationalized in two ways, i.e. by including (a) participants who have filled out the treatment goals and opened the standard modules of the intervention and (b) participants who have completed the intervention according their therapist.

Second, as the primary outcome consists of the mean CIS-fatigue score across T1 and T2, the extent to which our result would change if based on a single time point will be explored. Therefore, the analysis with the CIS-fatigue score at T1 as a dependent variable and with the CIS-fatigue score at T2 as a dependent variable adjusted for CIS-fatigue score at baseline using analysis of covariance will be repeated. For each of the time points Cohen’s d effect sizes will be calculated.

Third, the extent to which dyspnoea at T0, disease severity, time since diagnosis of COVID-19, age and sex have an impact on the primary outcome will be explored, and whether this impact differs between CBT and care as usual. These analyses will be conducted by including these variables and their interaction-terms with condition as covariates in the mixed linear models.

Fourth, missing values will be replaced with multiple imputation using chained equations and the data will be reanalysed. The imputation model will include all baseline sociodemographic and clinical characteristics assessed at baseline and follow-up measurements. A total of five data sets will be imputed and pooled according to Rubin’s rule.

Secondary outcomes will also be analysed according to intention-to-treat. For T1 and T2, it will be determined if there is a clinical meaningful improvement in fatigue, defined as a RCI [84] of more than 1.96 and a decrease of the fatigue level to a normal range (i.e. a score of < 35 on the CIS-fatigue). For secondary outcomes that are dichotomous, separate logistic regression analysis will be done for T1 and T2. For secondary outcomes that are continuous (i.e. physical functioning, work and social adjustment, somatic symptoms, cognitive symptoms), differences between CBT and care as usual will be analysed using mixed linear models as described above.

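### Referral to CBT after T2 in the care-as-usual arm hangs on the same CIS-fatigue score and cut that define the T2 dichotomous fatigue outcomes; a cheap change would separate the two

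*Protocol article*

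**What the plan says.** **Referral rule.** In the Care as usual section, participants with "a score of ≥ 35 on the CIS-fatigue at T2, and voice a care need can be referred for CBT for severe fatigue". The Expert Centre for Chronic Fatigue provides this treatment. The Procedure section describes the same offer, on ethical grounds, as one in which "participants from the care as usual arm are offered referral for existing CBT for chronic fatigue after the follow-up assessment (T2"), and attaches no score to it.

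**Outcomes on the same score.** Primary and secondary objectives lists, for T1 and T2 separately, "caseness as defined by a CIS-fatigue score of ≥ 35", and chronic fatigue as that caseness plus a self-reported duration of at least 6 months. Statistical analyses defines clinically meaningful improvement as an RCI above 1.96 together with "a decrease of the fatigue level to a normal range (i.e. a score of < 35 on the CIS-fatigue").

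**Who reports it.** Outcome measures: "Outcome measures consist of self-reported questionnaires, which are assessed at T0, T1, T2 and T3". Randomisation: "Due to the nature of the intervention, blinding to allocation is not feasible".

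**Where participants meet the scale.** The Participants section says the CIS fatigue subscale "is used for inclusion criterion c, to screen for the presence of severe fatigue". The Recruitment section says visitors to the study website can "fill out a brief test to check whether they fulfil inclusion criteria".

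**The concern.** An outcome that participants report about themselves should not also decide what care they get next, least of all in one arm of an open trial. Here a care-as-usual participant who wants CBT and would otherwise score just below 35 at T2 has, under the Care as usual rule, a reason to report slightly worse fatigue. A CBT participant has no matching reason, because the offer is made to the care-as-usual arm.

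If that reason acts, it acts in one direction. T2 caseness in care as usual goes up and the improvement outcome goes down, and both changes look like benefit from CBT. The outcomes at stake are three stated secondary objectives at T2. The T1 versions, SF-36 physical functioning, WSAS, PHQ-15 and CIS concentration do not gate referral.

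**Working it through.** **1. The plan's own figure.** Inputs from Sample size calculation: difference 6, SD 12, T1–T2 correlation 0.4, two-sided 0.05, power 80%, dropout 20%.
- SD of the T1/T2 mean = 12 × √((1 + 0.4)/2) = 10.04.
- n per arm = 2 × (1.96 + 0.84)² × 10.04² / 6² ≈ 44. With the stated 45 per arm, power is 0.81.
- 45/0.8 = 56.25, rounded up to 57 per arm, 114 in total.

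The sample size reproduces and is not in question.

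**2. Overlap of the referral rule and the T2 outcomes.**

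| Use | Score | Visit | Condition |
|---|---|---|---|
| Referral (Care as usual) | CIS-fatigue | T2 | ≥ 35 and a voiced care need |
| Referral (Procedure) | none stated | after T2 | none stated |
| Caseness | CIS-fatigue | T1, T2 | ≥ 35 |
| Chronic fatigue | CIS-fatigue | T1, T2 | ≥ 35 and duration ≥ 6 months |
| Clinical improvement | CIS-fatigue | T1, T2 | < 35 and RCI > 1.96 |

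At T2 the chronic fatigue outcome is nearly the same variable as caseness. Entry is at least 3 months after diagnosis or discharge, T1 is 19 weeks (4.4 months) after randomisation and T2 is 6 months later: 3 + 4.4 + 6 = 13.4 months. Fatigue present since COVID-19 therefore meets the duration condition automatically.

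**3. Illustration of size.** The document gives SD 12 and 45 analysed per arm. It gives no T2 mean and no rate of strategic reporting. Assumptions: care-as-usual T2 mean m of 36, 40 or 44; normal scores rounded to integers; a share s (10% or 50%) of those who would score 30 to 34 report 35 instead.
- Caseness p = 1 − Φ((34.5 − m)/12).
- Band b = Φ((34.5 − m)/12) − Φ((29.5 − m)/12).
- Rise in caseness = s × b.
- Shift in the T1/T2 average = s × b × (mean gap to 35)/2, because only T2 is affected.

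| m | p | b | Mean gap | Rise, s = 10% / 50% | Extra cases of 45 | Odds multiplied by | Primary shift (points) |
|---|---|---|---|---|---|---|---|
| 36 | 55.0% | 15.6% | 2.95 | 1.6 / 7.8 | 0.7 / 3.5 | 1.06 / 1.38 | 0.02 / 0.12 |
| 40 | 67.7% | 13.3% | 2.89 | 1.3 / 6.6 | 0.6 / 3.0 | 1.06 / 1.38 | 0.02 / 0.10 |
| 44 | 78.6% | 10.1% | 2.84 | 1.0 / 5.0 | 0.5 / 2.3 | 1.06 / 1.39 | 0.01 / 0.07 |

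Worked example at m = 40, s = 50%: 0.50 × 13.26% = 6.63 points, so 67.7% becomes 74.3%. The primary shift is 0.0663 × 2.89/2 = 0.096 points. The largest shift in the table, 0.12, is 2% of 6.

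Each participant who moves to 35 can lose at most one improvement, so the fall in the improvement outcome lies between zero and the rise in caseness.

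**4. Timing.** Recruitment began in November 2020 (Trial status). 1 November 2020 + 19 weeks = 14 March 2021; + 6 months = mid-September 2021, the earliest possible T2. The register search is dated July 2021 (Trial search), so T2 data collection had probably not begun when the article was submitted.

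**The case against.** The strongest objection is that the mechanism is undocumented. Bias requires care-as-usual participants to know or guess that the T2 score decides referral, and the article nowhere says they are told. What they are told belongs in the information letter and consent form, which are not shown. Completing the CIS at screening does not reveal the cut, and the website test is not said to show the scale or a threshold. The Procedure section describes an offer without a score; a participant who hears that version sees no gate. **This stands**, and it is why the effect may be zero.

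The gate is also soft. A care need must be voiced as well, the wording is permissive, and care as usual leaves other treatment open. Offering CBT for severe fatigue to those still above the trial's own cut for severe fatigue is clinically coherent. **These points stand too**, and they weaken the incentive.

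Two stronger readings are tempting. One is that T2 reporting in care as usual is in fact distorted; the document gives no evidence for that. The other is that the primary result is at risk because T2 CIS-fatigue is half of the T1/T2 average. A care-as-usual T2 mean raised by 1 to 3 points would move the average by 0.5 to 1.5 points, but nothing in the document supports a rise of that size. Movement of people just under the cut gives at most 0.12.

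What the objection does not remove is the stated rule itself. It links one arm's access to CBT to an unblinded outcome, and it differs from the Procedure section.

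**Conclusion.** The point holds as a conditional design weakness: minor, with low confidence. The overlap of scale, cut and visit is plain in the text, and the direction of any bias is clear: towards CBT, on the T2 dichotomous fatigue outcomes only. Whether any bias arises depends on what participants know or expect, which the article does not settle.

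The rise of 1.0 to 7.8 percentage points in care-as-usual caseness (0.5 to 3.5 participants of 45, odds multiplied by 1.06 to 1.39) rests on an assumed T2 mean and an assumed share of movers. Only the SD of 12 and the 45 per arm come from the protocol. The figures show scale and are not an estimate. The effect on the primary contrast is negligible, and the T1 and continuous secondary outcomes do not gate referral.

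**What to change.** Bring the Care as usual section into line with the Procedure section:
- Offer referral after T2 on a voiced care need, recorded once the T2 questionnaires are closed, with no reference to the T2 CIS-fatigue score.
- Let the treating centre apply its own severity criterion at intake.
- State in the T2 invitation that T2 answers do not decide access to care.

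The cost is one sentence in the procedure and one in the invitation. The ethical offer is kept, and a voiced care need is already required. The downside is that a few referred participants may be screened out at the centre's intake. No sample size or analysis changes. On the article's dates, the change could probably have been made before the first T2 assessment.

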### Randomisation

Allocation of participants to either CBT or care as usual is stratified based on (1) illness severity during the acute stage of COVID-19 (no admission to hospital; admitted to hospital, not on the intensive care unit (ICU); ICU during hospitalisation) and (2) dyspnoea based on the Medical Research Council (MRC) [59] score (< 3 vs. ≥ 3). This is because dyspnoea might influence the response to CBT by interfering with the graded activity module. A web-based randomisation programme in Castor EDC [60] is used to generate the randomisation sequence. The allocation ratio is 1:1. Block-randomisation with randomly selected block sizes (i.e. 2, 4 or 6) is used. The randomisation is performed by a research assistant in the presence of the participant who is on the phone. The research assistant, the researcher and the participants are blinded to the allocation sequence. Due to the nature of the intervention, blinding to allocation is not feasible. Data will be analysed by an independent statistician using a data file which is blinded for treatment allocation.

### Outcome measures

Outcome measures consist of self-reported questionnaires, which are assessed at T0, T1, T2 and T3. See Table 3 for the measurements at all time points. The questionnaires are administered online using Castor EDC [60]. Participants receive an e-mail with a personal link to fill out the questionnaires. For optimal retention, participants are contacted by the research assistant if they have not completed the questionnaires within one week. When participants are not willing to complete all measurements at T1, T2 and/or T3, they are asked to at least fill out the CIS-fatigue [38], which is the primary outcome measure. At T0 and T1, data on physical activity level and sleep are also gathered by using an actigraph and completing a sleep diary.

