### Secondary outcomes

*Limitations in physical functioning* are assessed by the subscale physical functioning of the SF-36 [40] which consists of ten items scored on a 3-point scale. The weighted subscale score ranges from 0 to 100, with a higher score indicating less limitations. A score of ≤ 65 is indicative of substantial limitations in physical functioning [63]. The SF-36 is a reliable and valid instrument [64].

*Social disability* is assessed by the WSAS [41, 65] which consists of five items assessing different domains of functioning, e.g. work and social leisure activities, scored on an 8-point Likert scale. A score of ≥ 10 is indicative of significant functional impairment [41, 65]. The WSAS is a reliable and valid instrument [41, 65.

*Somatic symptom severity* is assessed by the somatic symptoms scale of the Patient Health Questionnaire (PHQ) [66]. The PHQ-15 consists of 15 items referring to somatic symptoms. Each symptom is scored on a 3-point scale with scores of 5, 10 and 15 indicate low, medium, and high symptom severity. Research supports the reliability and validity of the PHQ-15 [66].

*Problems concentrating* are assessed by the subscale concentration of the CIS which consists of five items scored on a 7-point Likert scale. The scores range from 5 to 35, with a higher score indicating more difficulties in concentrating.

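### The four continuous secondary outcomes can be missing at visits where current fatigue is known, and no planned analysis of them uses that fatigue score

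*Protocol article*

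**What the plan says.** All references are to the Method part of the protocol article.

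- **Outcome measures** sets a minimum return for participants who will not complete everything at T1, T2 or T3: "they are asked to at least fill out the CIS-fatigue [38], which is the primary outcome measure".
- **Secondary outcomes** names four separate instruments: SF-36 physical functioning, WSAS, PHQ-15 and problems concentrating. The last "are assessed by the subscale concentration of the CIS which consists of five items", which are distinct from the eight CIS-fatigue items. None is part of the minimum return.
- **Statistical analyses** says that for the continuous secondary outcomes, "differences between CBT and care as usual will be analysed using mixed linear models as described above". The model described there has condition, time, their interaction, a random intercept and a baseline score.
- The same section plans chained-equation imputation whose model includes follow-up measurements. It is the fourth of four sensitivity analyses, all introduced as tests of the robustness of the primary analysis.
- **Primary and secondary objectives** defines chronic fatigue as a CIS-fatigue score of 35 or more together with "self-reported duration of fatigue of 6 months or longer at T1 and T2 separately".

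**The concern.** The short form protects the primary outcome at the expense of the others. A participant who returns only CIS-fatigue contributes nothing to the four continuous secondary outcomes at that visit, yet the variable most likely to explain both the refusal and the missing score has just been recorded. The secondary models do not use it. The one planned method that could use it is attached to the outcome that the short form already protects.

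Refusing a long questionnaire set may well be related to how tired someone is that week. Allocation is unblinded and only one arm is in contact with a therapist, so similar behaviour in both arms cannot be taken for granted. If behaviour differs, the comparisons of functioning, somatic symptoms and concentration are distorted although the information needed to correct them is in the data set.

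A smaller point concerns chronic fatigue. On CIS-fatigue alone, a score below 35 settles that the participant is not a case, whereas a score of 35 or more leaves the duration part open.

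**Working it through.** **The plan's own figures.** The article states no short-form rate. Its only related figure is the 20% dropout in the sample size, which is not in dispute. Effective SD = 12 × √((1 + 0.4)/2) = 10.04, which gives 43.95, so 44 per arm by normal approximation. At 45 per arm, power is 0.801 (noncentral t). 45/0.8 = 56.25, so 57 per arm and 114 in total.

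**What is lost.** Of the seven secondary objectives, four (the continuous outcomes) lose the visit. One (chronic fatigue) is open only for scores of 35 or more. Two (caseness; caseness plus reliable change) remain observed.

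**Continuous outcomes, two-visit check.** A large-sample simulation (60,000 per arm) fitted the specified random-intercept model with the outcome's own baseline.

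Assumptions:
- true effect -0.50 SD, which is -4 points at a WSAS SD of 8;
- same-visit correlation with CIS-fatigue 0.5 or 0.7;
- correlation of 0.4 between occasions (the article gives 0.4 for CIS-fatigue at T1 and T2);
- where short-form use depends on fatigue, log-odds of 1 per SD of current fatigue;
- short-form use at about 7–21% of visits.

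| Short-form use depends on fatigue | Specified model (SD units) | × 8 (WSAS points) |
|---|---|---|
| in neither arm | -0.490 to -0.500 | -3.9 to -4.0 |
| equally in both arms, equal rates | -0.496 to -0.503 | -4.0 |
| in usual care only | -0.461 to -0.400 | -3.7 to -3.2 |
| in opposite directions (more fatigued in usual care, less fatigued in CBT) | -0.428 to -0.299 | -3.4 to -2.4 |

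Chained-equation imputation with CIS-fatigue among the predictors gave -0.490 to -0.505 in every row. Dependence in CBT only mirrors the third row: -8 - (-3.69) = -4.31 and -8 - (-3.20) = -4.80.

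**One-visit check.** A separate baseline-adjusted simulation (400,000 per arm, 10–20% short-form use) gave -4.31 to -4.81 for dependence in CBT only and -3.15 to -3.67 for usual care only. A further run of the usual-care case reached -3.05. Using same-visit CIS-fatigue gave -3.97 to -4.03 throughout. Taken together, dependence in one arm gives roughly -3.1 to -4.8.

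**Chronic fatigue.** Let p be the true proportion and q the short-form share, taken as equal for cases and non-cases. If short-form non-cases are kept and short-form scores of 35 or more are dropped, the analysed proportion is p(1 - q)/[(1 - q) + q(1 - p)]. With p = 0.60 in both arms:
- q = 0.15 (CBT): 0.51/0.91 = 56.0%
- q = 0.05 (usual care): 0.57/0.97 = 58.8%

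The spurious difference is 2.7 points, and the odds ratio is 0.85/0.95 = 0.89 instead of 1. With equal shares the odds ratio is unchanged, but both proportions are too low.

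**Can duration be inferred?** Entry is at least 3 months after diagnosis or discharge, and T1 is 19 weeks after randomisation: 19 × 7/30.44 = 4.4 months. The minimum is therefore about 7.4 months at T1 and, 6 months later, 13.4 months at T2. A participant fatigued without a break since COVID-19 has passed 6 months at both visits.

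**The case against.** **This is detail for the analysis plan.** A journal article condenses its protocol, and secondary models without an auxiliary variable are common. That is fair as far as silence goes. But the article does fix the collection rule and the secondary model, and it does tie the imputation to the primary analysis. The point rests on those three statements taken together.

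**The mixed model already handles missing data.** This stands in part. A reader might infer that the secondary models are valid only if short-form use is unrelated to current fatigue. That is too strict: a likelihood-based model needs missingness at random given arm, baseline and the score observed at the other visit. Only dependence on fatigue beyond those terms matters, and the treatment comparison shifts only when it differs between arms.

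**The direction is unknown.** This stands. It is tempting to expect bias in favour of CBT, from unimproved CBT participants choosing the short form. Nothing in the article supports that over the reverse, and dependence in usual care alone biases against CBT. Estimates beyond about -5 require fatigue to drive short-form use in opposite directions in the two arms.

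**The loss may be smaller than feared.** The rule sets a minimum, so some reluctant participants may return more. Table 3 is not shown, so where duration is asked cannot be seen.

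**Chronic fatigue can mostly be derived.** This largely stands. A reader might infer that short-form responders scoring 35 or more cannot be classified. By the article's own timing most of them can, with remission followed by relapse as the exception. The 2.7 points also rest on an assumed 15% versus 5% split, and on dropping cases while keeping non-cases, which the article does not say will happen. For scale, the standard error of that difference with 57 per arm is √(2 × 0.6 × 0.4/57) = 9.2 points.

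**Conclusion.** The point holds in a limited form. Known fatigue scores go unused at visits where the four continuous secondary outcomes are missing, and the planned method that could use them is confined to the primary analysis. The resulting bias is conditional: it needs short-form use that depends on current fatigue beyond baseline and the other visit, and that differs by arm. It can then go either way. Under the assumed inputs (10–20% short-form use, WSAS SD 8, true difference -4, correlations of 0.5–0.7, log-odds of 1 per SD), dependence in one arm gives about -3.1 to -4.8. Dependence and rates that are equal across arms give no visible bias. The article gives neither a short-form rate nor evidence of a difference between arms, so these figures show what could happen and do not predict what will.

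The chronic-fatigue part is minor and needs only a stated classification rule. The primary outcome, caseness, and caseness with reliable change do not depend on the missing instruments.

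**What to change.** 1. Extend the chained-equation imputation already planned under Statistical analyses to SF-36 physical functioning, WSAS, PHQ-15 and CIS concentration, as a sensitivity analysis. Use condition, the baseline score, the other visit's score and CIS-fatigue at T1 and T2 as predictors.
2. Report the number of CIS-only responders by arm and visit, so that readers can judge whether the issue arises.
3. State how chronic fatigue is classified when only CIS-fatigue is returned. Impute duration, or derive it from entry data where fatigue has been continuous. Do not keep short-form scores below 35 as non-cases while dropping those of 35 or more.

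The cost is slight extra analysis on data already collected. Sample size, the primary analysis and the assessment schedule do not change.
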